# “EspaiJove.net”- a school-based intervention programme to promote mental health and eradicate stigma in the adolescent population: study protocol for a cluster randomised controlled trial

**DOI:** 10.1186/s12889-018-5855-1

**Published:** 2018-07-31

**Keywords:** Mental health, Promotion, Prevention, Stigma, Adolescence, School, Intervention, Mental health literacy

## Abstract

**Background:**

One half of adults who develop any mental disorder do so during adolescence. Previous literature showed that Mental Health Literacy (MHL) interventions impact mental health knowledge, reduce the associated stigma, and promote help-seeking among the adolescent population. However, evidence for the effectiveness and cost-effectiveness of these programmes remains inconclusive. The aim of this paper is to present a study protocol that evaluates the effectiveness of the “EspaiJove.net” programme. “EspaiJove.net” consists of a universal MHL intervention designed to promote mental health knowledge, increase help-seeking, reduce the stigma associated with mental illness, and prevent mental disorders in Spanish school settings.

**Methods:**

A school-based clustered randomised controlled trial (cRCT) design with 12 months of follow-up. **Subjects:** At least 408 secondary school students who attend the 3rd year of E.S.O (Compulsory secondary education for 13- to 14-year- olds) will be recruited from 8 schools within Barcelona city, Catalonia (Spain). **Intervention:** A dose-response intervention will be delivered with 4 arms: 1) Sensitivity Programme (SP) in Mental Health (1 h); 2) Mental Health Literacy (MHL) Programme (6 h); 3) MHL plus first-person Stigma Reduction (MHL + SR) (7 h); 4) Control group: waiting list.

**Primary outcomes:** 1) MHL: EspaiJove.net MHL Test (EMHLT); 2) Stigma: Reported and Intended Behaviour Scale (RIBS) and Community Attitudes toward the Mentally Ill (CAMI). **Others outcomes:** 1) Acceptability of intervention; 2) Mental health symptoms and emotional well-being (SDQ); 3) States of Change Scale (SCS); 4) Bullying and Cyberbullying; 5) Quality of life (EQ-5D); 6) Help seeking and use of treatment; 7) Health benefits.

**Discussion:**

Results would be informative for efforts to prevent mental disorders and promote mental wellbeing in secondary school students.

**Trial registration:**

NCT03215654 (date registration July 12, 2017).

**Electronic supplementary material:**

The online version of this article (10.1186/s12889-018-5855-1) contains supplementary material, which is available to authorized users.

## Background

The World Health Organisation (WHO) recognises mental disorders as one of the major health problems worldwide and as one of the biggest contributors to the global burden of disease [1]. With respect to the prevalence of mental disorders among adolescents and young adults, anxiety and depression are the most prevalent problems, there being a 12-month prevalence of 8% for anxiety and 4–5% for depression [2–4].

Mental disorders are a serious public health problem. It is estimated that 75% of all people suffering from a mental health disorder experienced onset before the age of 25 [5, 6], and 50% during adolescence [7]. Therefore, it coincides with the person’s crucial evolutionary moments which could represent a significant problem for the biological, psychological and social development of adolescents and young people.

Unfortunately, the prevalence of depression in adolescents and young adults has increased in the last few years, with a rise in the number of untreated young people [8]. Furthermore, young people delay their first visit to a health professional when suffering of a mental disorder. There is evidence that stigma and a lack of knowledge have been associated with a chronic delay in help-seeking [9, 10].

A systematic review of barriers and facilitators for help-seeking in young people found that one of the key barriers was stigma [11]. Stigma has a disabling impact on the individual’s sense of self, including diminished self-esteem, self-value and confidence [12]. Studies have shown a link between stigma, not seeking help and non-adherence to treatments [13].

A.F. Jorm introduced the concept of “Mental Health Literacy” (MHL) [14] in 1997, defined as a set of “knowledge and beliefs about mental disorders that aid recognition, management or prevention”. Therefore, MHL involves: a) the ability to recognise the development of mental disorders to facilitate early help-seeking behaviours; b) knowledge and beliefs about risk factors, the causes of mental disorders and how to prevent them; c) knowledge of how to get professional help, effective available treatments, and effective self-help strategies; d) attitudes that facilitate recognition and an adequate search for help; and e) knowledge and skills to provide first aid in mental health and support to other people. Also, the author proposed a training programme on mental health delivered to the general population to improve MHL interventions [9]. These studies point out the need to increase MHL due to the high number of mental disorder cases among young people and the low precocious diagnosis [15], the need to carry out these types of interventions in school settings [16–18] and the importance of working together in a coordinated way among the different services (educational centres, mental health services and community health) so as to benefit the health of young people [19].

Some MHL programmes for adolescents and young people have been developed in recent years in several countries [20–24]. These programmes suggest an improvement in mental health knowledge, the self-recognition of mental disorders among young people, and an improvement in facilitating monitoring in help-seeking and reducing mental health-related stigma immediately after an intervention [12, 13, 25–27]. However, recent systematic reviews and meta-analyses have shown that there is insufficient evidence about the positive impact of the school-based MHL interventions, and therefore more studies with better methodological designs are needed [28, 29].

The *EspaiJove.net**: a space for mental health* (EspaiJove.net) programme is a universal MHL programme which aims to promote mental health, prevent mental disorders, facilitate help-seeking behaviours and eradicate related stigma among secondary school students (between 11 and 18 years old) within the Spanish context. The programme integrates a multi-modal intervention that combines taught classes and training activities among schools with the use of Information and Communication Technology (ICT) such as the website www.espaijove.net and online consultation [30].

During the last five academic courses (2012/13 to 2016/17), 14,139 young people have been trained, of whom 7698 completed a questionnaire after the training activity. Despite there being widespread acceptability and satisfaction with the intervention (91% found it interesting and useful and 94% recommended the activity), a lack of robust evidence in MHL among the Spanish population and confirmation of good results meant that it was found that the EspaiJove.net programme needed to be evaluated.

In this article, we present a study protocol of a cluster randomised controlled trial that intends to evaluate the effectiveness of the universal school based-intervention “EspaiJove.net” programme. The main objective of the study is to evaluate whether the “EspaiJove.net” intervention has a short- (2 weeks) and long-term (6 and 12 months follow-up) impact on increasing MHL and reducing the related stigma among students who attend the 3rd year of E.S.O (Compulsory secondary education) or 9th grade (13- to 14-year- olds) in Barcelona, Spain. Furthermore, this study will assess the dose-response relationship for these outcomes. A secondary objective is to analyse the impact of the interventions on help-seeking behaviours, mental health symptoms and emotional well-being, bullying and cyber-bullying behaviours and health-related quality of life (HRQoL).

The primary hypothesis to be tested will be that: participants in the intervention groups (Sensitivity Programme (SP), MHL programme and MHL + SR programme) will increase their knowledge on mental health and mental disorders, and reduce the stigma associated with mental illness showing a dose-response relationship compared to a waiting list control group immediately after 2 weeks, 6 months and 12 months post-intervention.

A secondary hypothesis to be tested will be: participation in the intervention groups (SP, MHL and MHL + SR) will reduce mental health symptoms, increase emotional well-being and help-seeking behaviours, reduce bullying and cyberbullying at school, and improve HRQoL immediately after 2 weeks, 6 months and 12 months post-intervention, compared to a waiting list control group.

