## Methods

### Study design

The study is a multicentre and school-based clustered randomised controlled trial (cRCT) with four intervention arms. Eligible schools are randomly allocated either to an intervention group or a control group (see Fig. 1). Data will be collected at baseline, and at 2 weeks, 6 months and 12 months following the intervention. Each school will participate in the study for two academic years from September 2017 to September 2019.

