### Sample size

A power analysis was conducted to determine the appropriate sample size. According to a previous RCT of MHL [32], assuming that we wanted to be able to identify a minimal difference of 0.18 effect size in MHL scores after the intervention. To detect differences in each group with one-way analysis of variance (ANOVA) that corresponds to a small effect size (0.18), with an alpha risk of 0.05, and a power of 80%, the adequate sample size required for this study in each group will be 85 students (*n* = 340). Assuming an attrition rate of 20% during the 12 months of follow-up after the intervention, we estimate that a total sample of 408 students will be required.

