### Primary outcomes

The primary outcomes of this study are mental health literacy (MHL) and stigma associated with mental illness.

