### Statistical analysis

To analyse the effectiveness of the EspaiJove.net intervention, an experimental design will be created to evaluate the programme, randomised by clusters (schools) and with a control group on the waiting list. The statistical analyses to be performed will be as follows. A description of the sociodemographic variables of the sample at baseline will be done through a univariate analysis of the selected variables from the total sample and stratified by type of intervention. Then, to evaluate the effectiveness of all programmes and to achieve statistical significance for all outcomes after the intervention, an unadjusted bivariate primary analysis will be performed. Data scores after the intervention will be analysed with ANOVA, assuming that the baseline data will be similar due to the randomisation process across groups. Finally, a multivariate and adjusted analysis, as necessary, will be employed to evaluate the effectiveness of those programmes so as to achieve statistical significance after the intervention. Data will be analysed with Generalised Equation Estimates (GEE) to assess the efficacy of the intervention. This statistical model is appropriate for longitudinal clustering analyses since this study design (schools) will allow us to consider the individual data correlation within the same cluster group. Analyses will be based on an intention-to-treat analysis.

We will also examine relative and absolute risk reduction, (RRR) and (ARR), respectively. Additionally, to analyse the acceptability and satisfaction of each programme, a descriptive analysis will be performed to observe the percentage of acceptability and satisfaction. Statistical analyses will be performed using the SPSS [48].

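### The primary hypothesis is an ordered dose-response on three scales at three times, but the named primary test ignores arm order and no success rule links the scales and times

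*Protocol article*

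**What the plan says.** All references are to the protocol article.

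- **Hypothesis.** In the Background section, the three programmes are expected to raise knowledge and lower stigma, "showing a dose-response relationship compared to a waiting list control group immediately after 2 weeks, 6 months and 12 months post-intervention". The main objective adds: "Furthermore, this study will assess the dose-response relationship for these outcomes".
- **Outcomes.** Under Primary outcomes: "The primary outcomes of this study are mental health literacy (MHL) and stigma associated with mental illness". The abstract gives the knowledge test (EMHLT) as the first, then "2) Stigma: Reported and Intended Behaviour Scale (RIBS) and Community Attitudes toward the Mentally Ill (CAMI"). Table 3 lists the same three measures as primary, using the authoritarianism subscale of CAMI. No scale leads.
- **Times.** Under Study design: "Data will be collected at baseline, and at 2 weeks, 6 months and 12 months following the intervention". No time leads.
- **Sizing.** The Sample size section uses a one-way ANOVA across the groups, "that corresponds to a small effect size (0.18"), "with an alpha risk of 0.05, and a power of 80"%. This leads to 85 per group, 340 in all.
- **Analysis.** In the Statistical analysis section the primary analysis is unadjusted, "to evaluate the effectiveness of all programmes and to achieve statistical significance for all outcomes after the intervention", with post-intervention scores compared by ANOVA. An adjusted analysis by GEE follows where needed, allowing for correlation within schools. Neither is given a trend, an ordered contrast or a dose term.

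**The concern.** There are two mismatches between the claim and the method.

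First, a significant four-group ANOVA says only that the four means are not all equal. It gives the same answer if one hour of teaching does better than seven. A trial run as written could report a significant primary result without having tested the dose-response that its primary hypothesis asserts.

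Second, the hypothesis spans nine scale-by-time results, while the design calculation uses its 0.05 and its 80% once. Without a success rule, a reader of the results cannot tell whether one significant result in nine confirms the hypothesis or eight in nine fail to. The first reading loosens the error rate. The second leaves the joint claim without a power statement.

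**Working it through.** **Inputs.** Four arms, 1:1:1:1 (Recruitment process). 85 per arm, effect size 0.18, alpha 0.05, power 80%, one-way ANOVA (Sample size). Three primary scales (abstract, Table 3). Three post-intervention times (Study design). Programme hours 0, 1, 6, 7 (Table 1). Means below are in SD units. Nothing here allows for clustering.

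**Step 1. Reproduce the plan's figure.** Read 0.18 as Cohen's f. For the omnibus F test, λ = N·f² = 340 × 0.18² = 11.02 on (3, 336) df, with critical value 2.63. Power at 85 per arm is 79.9%, and 86 per arm gives 80.5%. The stated 85 is therefore reproduced to within one student per arm. Read as a two-group standardised difference, 0.18 would need 485 per group, so f is the reading that fits. The sample size corresponds to one omnibus test at an unsplit 0.05.

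**Step 2. Does the test see order?** λ depends only on the squared deviations of the means, so permuting the arms leaves it unchanged. Compare a linear contrast with c = (−3, −1, 1, 3), δ = Σcμ / √(Σc²/85), two-sided 5%, 336 df.

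| Means (control, SP, MHL, MHL+SR) | Omnibus F | Trend contrast |
|---|---|---|
| Rising: −0.241, −0.080, 0.080, 0.241 | 79.9% | 91.1%, upward (δ = 3.32) |
| Reversed: 0.241, 0.080, −0.080, −0.241 | 79.9% | 91.1%, downward |
| Scrambled: −0.080, 0.241, −0.241, 0.080 | 79.9% | 5.0% (δ = 0) |

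**Step 3. How far does the trend's advantage depend on shape?**

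| Means | Scores | Omnibus F | Trend contrast |
|---|---|---|---|
| 0, 0.161, 0.322, 0.483 | equal | 80% | 91% |
| 0, 0.058, 0.345, 0.403 (linear in hours) | 0, 1, 6, 7 | 77% | 90% |
| 0, 0.416, 0.416, 0.416 (first step only) | equal | 80% | 73% |
| 0, 0, 0, 0.416 (last step only) | equal | 80% | 73% |
| 0, 0, 0.36, 0.36 (middle step only) | equal | 80% | 84% |

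The trend gains when the response is roughly linear and loses when a single end step carries everything. In those end-step cases it still rejects 73% of the time although the full ordering is false, so a significant trend alone does not establish control < SP < MHL < MHL+SR.

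**Step 4. Nine results, one alpha.** 3 scales × 3 times = 9.

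- *Any one counts, each tested at 0.05 (assumed).* Independent: 1 − 0.95⁹ = 0.370. By simulation with assumed correlations, 0.33 (0.2 between scales, 0.5 between times) falling to 0.19 (0.8 for both). For three scales at one time, independent: 1 − 0.95³ = 0.143.
- *Same rule with a Bonferroni split.* Over nine, 0.05/9 = 0.0056: omnibus power at 85 per arm falls from 80% to 51%, and 80% needs 134 per arm (4 × 134 = 536 evaluable). Over three, 0.05/3 = 0.0167: power is 66%, and 110 per arm (440 evaluable) are needed.
- *All must succeed.* Type I error for the joint claim stays at or below 0.05. With 80% power for each result, joint power is at most 80%, and 0.8⁹ = 13% if the nine were independent.

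**The case against.** **The plan also has a GEE.** It does, it allows for schools, and it could carry a dose contrast. But the article places it after the analysis it calls primary, uses it where needed, and gives it no dose term. So a reader should not infer that the plan has no model able to test order. What stands is that no stated analysis does so.

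**Contrasts and alpha sharing belong in the analysis plan, which is not shown.** The coding of contrasts may well sit there. But this article itself fixes the hypothesis, the primary test and the test used for sizing, and these do not match one another.

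**The error rate may not be inflated at all.** This is fair. The hypothesis joins knowledge with stigma and lists all three times, and the analysis text speaks of all outcomes. If that means all must succeed, alpha is held. The text does not settle it.

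**A trend test is not a proof of order, nor always stronger.** This also stands, as Step 3 shows. The seventh hour is a first-person presentation and so differs in content as well as dose, which weakens a purely linear reading. A trend contrast therefore needs supporting contrasts beside it.

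**Naming EMHLT at 2 weeks as the single primary result would re-rank the stated aims.** Correct: 6 and 12 months and stigma are in the main objective. Which results lead is the sponsor's choice.

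**Conclusion.** The point holds in this form: the primary hypothesis is ordered, the primary analysis and the sizing test are insensitive to order, and no rule joins the three scales and three times. The order mismatch rests on the text alone and needs no assumption.

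The multiplicity figures are conditional. Up to 37% (about 19–33% under the assumed correlations) applies only if any one of nine tests at 0.05 would count as success. Under an all-must-succeed rule the cost is power instead.

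Two stronger readings are not supported. A reader might infer that every test is to be run at 0.05, but the article gives 0.05 once, as a sample-size input, and no per-test level. A reader might also count 27 arm-versus-control tests (3 × 3 × 3) and reach 1 − 0.95²⁷ = 75%. The Statistical analysis section specifies no such set, and independence cannot hold with a shared control arm and repeated measurement of the same students.

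The power comparison of 91% with 80% assumes evenly spaced means, f = 0.18 and 85 per arm. It turns to 73% against 80% if only the first or last step carries the effect. All these powers are before clustering.

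**What to change.** 1. Within the school-clustered model, prespecify a linear trend contrast across control, SP, MHL and MHL+SR, with its scores stated, as the test of the dose-response hypothesis.
2. Support it with each arm against control and with adjacent-arm contrasts. Include MHL+SR against MHL, because hour 7 adds different content. Claim the full ordering only if these agree.
3. State one success rule for the three scales and three times: a lead scale and time followed by a fixed sequence, an alpha split such as Holm, or all must succeed. The sponsor should choose, since the choice ranks the trial's aims.
4. Restate the power for that contrast and that rule, allowing for clustering.

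The cost is wording and a recalculation, with no new data collected. The downsides are small: fewer results can be called confirmatory, and some power is lost if the response is far from linear. The restated power may be below 80% at the planned size, and it is better to learn that before the analysis.

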## Methods

### Study design

The study is a multicentre and school-based clustered randomised controlled trial (cRCT) with four intervention arms. Eligible schools are randomly allocated either to an intervention group or a control group (see Fig. 1). Data will be collected at baseline, and at 2 weeks, 6 months and 12 months following the intervention. Each school will participate in the study for two academic years from September 2017 to September 2019.

**Fig. 1 Fig1:**
[figure not shown]
Schematic Illustration of the research design

The study has been designed in accordance with The Standard Protocol Items: Recommendations for Interventional Trials (SPIRIT) Statement for reporting a clinical trial protocol (see Additional file 1 for checklist) [31]. Trial registration NCT03215654.

### Sample

Eligible participants are students who attend the 3rd year of E.S.O (Compulsory secondary education) or 9th grade (13- to 14-year- olds) who consent to participating in the study. Potentially eligible schools include 191 public and private schools located in 8 districts within Barcelona city, Spain. Of these, only those schools that agree to participate in research allow accessibility and commit to the continuity of the project will be involved. Each school will be distributed by the number of classes for each arm, and several randomisations will be conducted for each strata (up to five classes x grade) (see Fig 2). The inclusion criteria are as follows: adolescent students who (1) currently attend the 3rd year of E.S.O (Compulsory secondary education) in a public or private school located in Barcelona city, Spain; and (2) sign the informed consent. Exclusion criteria are as follows: students who (1) have attended a workshop by “EspaiJove.net” prior to the study; (2) attend any special education school; (3) have special educational needs attending any school; and (4) do not understand Spanish and Catalan.

**Fig. 2 Fig2:**
[figure not shown]
Flow chart of participants

### Sample size

A power analysis was conducted to determine the appropriate sample size. According to a previous RCT of MHL [32], assuming that we wanted to be able to identify a minimal difference of 0.18 effect size in MHL scores after the intervention. To detect differences in each group with one-way analysis of variance (ANOVA) that corresponds to a small effect size (0.18), with an alpha risk of 0.05, and a power of 80%, the adequate sample size required for this study in each group will be 85 students (*n* = 340). Assuming an attrition rate of 20% during the 12 months of follow-up after the intervention, we estimate that a total sample of 408 students will be required.

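### The sample size counts 340 pupils as independent although 8 whole schools are randomised to four arms, so the stated 80% power is not delivered

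*Protocol article*

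**What the plan says.** The Sample size section of the protocol article gives a finished calculation. The aim is to "identify a minimal difference of 0.18 effect size in MHL scores after the intervention". The method is set out as "To detect differences in each group with one-way analysis of variance (ANOVA) that corresponds to a small effect size (0.18"). The significance level is 5% and the target power 80%. The result is that "the adequate sample size required for this study in each group will be 85 students", 340 in total. The last step is "Assuming an attrition rate of 20% during the 12 months of follow-up after the intervention", from which "we estimate that a total sample of 408 students will be required". The section mentions no ICC, design effect, cluster size or number of schools.

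The design is described elsewhere in the article. Study design: "Eligible schools are randomly allocated either to an intervention group or a control group". Abstract, Methods: pupils "will be recruited from 8 schools within Barcelona city". Recruitment process: allocation is 1:1:1:1 to four arms. Statistical analysis repeats that schools are the randomised clusters. It names an unadjusted ANOVA as the primary analysis, followed by a GEE chosen because it accounts for correlation within a cluster.

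**The concern.** Pupils in one school tend to resemble each other, so 42 pupils from a single school carry less information than 42 pupils sampled independently. The comparison between arms also rests on how much schools differ, and with 8 schools in four arms that is estimated from very few units. A calculation that ignores both overstates power. The article recognises the correlation when it chooses the GEE but does not carry it into the sample size.

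The effect size is a second problem. Calling 0.18 a minimal difference and a small effect invites the reader to think that two arms differing by 0.18 SD could be told apart. The number reproduces the sample size only as Cohen's f, which is a different quantity.

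At stake is how the result is read. Under an analysis that respects the schools, a null result could be taken as evidence of no effect when the trial had little chance of finding one. Under the unadjusted ANOVA the risk is the opposite: a significant result could reflect school differences alone.

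**Working it through.** **Inputs.** From the Sample size section: k = 4 groups, effect size 0.18, alpha 0.05, power 80%, 85 per group, N = 340. From the Abstract: 8 schools. From Recruitment process: 1:1:1:1, hence 8/4 = 2 schools per arm (derived, not stated). Pupils analysed per school: m = 340/8 = 42.5. The article gives no ICC, so 0.01 to 0.10 is assumed.

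**Reproducing the article's figure.** For a one-way ANOVA with independent pupils, the noncentrality is λ = f² × N = 0.18² × 340 = 11.02. The F test on 3 and 336 df then has power 0.799. The first size to reach 0.80 is 86 per group, so the stated 85 agrees. The recruitment target is 340 × 1.2 = 408, so that inflation is all for attrition. No clustering allowance is hidden in either number.

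**What 0.18 means.** Read as a standardised difference between two arms, 0.18 would need 485 per group, and 85 per group would have about 21.5% power before any clustering. Only Cohen's f reproduces 85. For four equal groups, f = 0.18 corresponds to a largest gap between arms of 2f = 0.36 SD (two arms high, two low) up to f × √8 = 0.51 SD (two extreme arms, two at the mean).

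**Adding the clustering.** Design effect DE = 1 + (m − 1) × ICC = 1 + 41.5 × ICC. Effective N = 340/DE. λ = 11.02/DE. Power is shown first with the design effect only, F(3, effective N − 4), then with school-level error df, F(3, 8 − 4 = 4). The difference between two arms detectable with 80% power on 4 df is 3.76 × √(2 × DE/85) SD, where 3.76 is the noncentrality that gives a two-sided 5% t test on 4 df 80% power.

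| Assumed ICC | DE | Effective N | Power, design effect only | Power, 4 df | Detectable difference between two arms, 4 df |
|---|---|---|---|---|---|
| 0.01 | 1.42 | 240 | 63% | 29% | 0.69 SD |
| 0.02 | 1.83 | 186 | 51% | 23.5% | 0.78 SD |
| 0.05 | 3.08 | 111 | 31% | 16% | 1.01 SD |
| 0.10 | 5.15 | 66 | 19% | 11% | 1.31 SD |

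Even at ICC = 0, the F test on 3 and 4 df has only 39% power.

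**Would more pupils in the same schools help?** As m grows without limit, λ tends to f² × 8/ICC. On 4 df, power then cannot exceed 74% at ICC 0.01, 45% at 0.02, 21% at 0.05 and 13% at 0.10. For 80% power with school-level df and 42.5 pupils per school, the totals needed are 16, 20, 32 and 48 schools.

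**The unadjusted ANOVA.** Simulated with 2 schools of 42.5 per arm and no true effect, an ANOVA that treats pupils as independent rejects about 14% of the time at ICC 0.01 and about 47% at ICC 0.05, against a nominal 5%.

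**The case against.** The fairest counter-argument is that the calculation matches the test it was made for. The article sizes an ANOVA and names an unadjusted ANOVA as primary. With a true f of 0.18 that ANOVA still rejects about 80% of the time at ICC 0.01 to 0.05. This is true, but it does so only because its false-positive rate is about 14% to 47%. A rejection rate bought that way is not 80% power at alpha 0.05. What stands is that, if the ANOVA were kept as the basis for inference, the main danger would be a false positive rather than a missed effect.

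Three other points have some force:

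- **The 4 df are the strict school-level benchmark.** The planned clustered model is a GEE, and much of the fall from 80% to 29% at ICC 0.01 comes from the df. The design-effect-only column does not depend on that choice, and it already contradicts 80%.
- **Two schools per arm is inferred.** The Sample section speaks of classes per arm and of randomisations within strata, which blurs the unit, but Study design and Statistical analysis both name schools. If classes were the unit (16 classes of about 21, assumed), design-effect-only power would still be about 71% at ICC 0.01 and 47% at 0.05.
- **408 is a minimum.** With 85 analysed pupils per school and ICC 0.01, design-effect-only power would reach 84%. That is twice the stated size, and on 4 df power would still be 42%.

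The gap cannot be put down to a condensed article or left to an analysis plan. The method, inputs and result are all published, and 85 is fully explained without a design effect.

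**Conclusion.** The concern holds. The stated 80% is the power of an individually randomised trial of 340 pupils, not of this one. At the stated size, any positive ICC takes the power of a valid analysis below 80%. Over the assumed ICC range of 0.01 to 0.10, power is 63% to 19% by the design effect alone and 29% to 11% with school-level degrees of freedom. The size of the shortfall depends on the assumed ICC, equal school sizes of 42.5 and two schools per arm; its direction does not depend on the ICC value chosen. The mislabelled effect size is a smaller matter of wording, but it makes the trial look more sensitive than even its own calculation supports.

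**What to change.** Withdraw the 80% power statement and rewrite the Sample size paragraph to:

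- state the number of schools per arm, the expected number of pupils analysed per school, and an ICC range with its source;
- give power, or the detectable difference, with DE = 1 + (m − 1) × ICC and 4 error degrees of freedom, for an analysis that accounts for schools and not for the unadjusted ANOVA;
- label 0.18 as Cohen's f and give the 0.36 to 0.51 SD gap between arms that it implies;
- say that comparisons of each arm with control will be reported as estimates with wide intervals, and that a non-significant result is not evidence of no effect.

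The cost is one rewritten paragraph and a much less favourable power figure. No extra schools are needed to correct the statement. If 80% power is still wanted, it has to come from more schools rather than more pupils per school.
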